### Statistical analysis

Two main analyses will be conducted investigating HRT use after diagnosis and immediately before diagnosis.

In the analysis of HRT use after diagnosis, patients will be followed from 6 months after cancer diagnosis to cancer-specific mortality (censored on death from other causes or end of follow-up). Consequently, patients who died from any cause in the first 6 months after cancer diagnosis will be excluded as it seems unlikely that HRT use after diagnosis could impact upon such deaths (in sensitivity analyses this duration will be varied, described later). HRT use will be modelled as a time varying covariate to avoid immortal time bias [36], i.e. patients will be considered non-users and then users after a lag of 6 months after their first HRT prescription. A lag is recommended in studies of medication use and cancer survival [37] as it moves the exposed period forward which is more likely to reflect when the medication will may have an impact. A dose-response analysis will be conducted by duration of use based upon daily defined doses (DDDs) and number of prescriptions. An individual will be considered a non-user prior to 6 months after first HRT use, a user of 0 to 1 year of prescriptions from 6 months after first prescription to 6 months after their 12th prescription (or 365th DDD) and a greater user after this time. Time-dependent cox regression models will be used to calculate hazard ratios (HRs), and 95% confidence intervals (CIs), for HRT use after cancer diagnosis adjusting for age, year, ethnicity, stage, cancer treatment, grade, comorbidities, prior hysterectomy/oophorectomy, medication use (as time-varying covariates) and deprivation. A two-stage analysis procedure using random effects models will be conducted to pool results across cohorts [38]. Separate analyses will be conducted by type and route of administration of HRT.

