In the analysis of HRT before diagnosis, cancer patients will be followed from diagnosis to cancer-specific mortality. HRT use will be identified in the 18 months before diagnosis excluding HRT use in the six months immediately before diagnosis, as depending upon the cancer drug use can increase in this period due to cancer symptoms [39]. Cox regression models will be used to calculate HRs and 95% CIs for cancer-specific death in HRT users compared with non-users. Age, year, ethnicity, comorbidities, prior hysterectomy/oophorectomy and medication use before diagnosis will be included in these cox regression models to calculate adjusted HRs and 95%CIs. Stage, grade and cancer treatments will be excluded from the models investigating HRT before diagnosis, as these could lie on the causal pathway. As before two-stage methods will pool results across cohorts.

A number of additional analyses will be conducted. First, the main analysis will be repeated additionally adjusting for characteristics not available in both cohorts e.g. family history, smoking and BMI (only available in Welsh data). An analysis will be conducted restricted to women over age 55 (i.e. post-menopausal women) and an analysis will be conducted widening the age groups to include younger women aged 18 to 40 (Scottish data). An analysis of HRT after diagnosis will be conducted using a new-user design i.e. restricting analyses to cancer patients who did not use HRT before diagnosis [40], and after adjustment for HRT before diagnosis. A separate analysis will be conducted investigating the timing of HRT initiation after cancer diagnosis. Analyses of HRT after diagnosis will be conducted varying the lag from 6 months to 1 and 2 years.

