The primary analysis strategy will be repeated for the secondary outcome of all-cause mortality and second cancers. A different analysis strategy will be used to investigate the secondary outcome of cardiovascular disease and VTE. In these analyses current use of hormone replacement therapy after cancer diagnosis will be modelled as a time-varying covariate. Patients will become a current user upon the date of each hormone replacement therapy prescription, and remain a user for the duration of the prescription, based upon the daily defined dose, plus 30 days to account for any residual effect. The exposure period from the end of one prescription plus 30 days to the start of the next will be allocated to past use. Cox regression models will then be used to calculate HRs and 95% CI for cardiovascular disease overall and by type comparing hormone replacement therapy current use and past use to non-users, adjusting for the confounders mentioned previously.

In general, multiple imputation will be used to impute missing values particularly for stage, smoking and BMI. As recommended cancer-specific death status and cumulative hazard will be included in imputation models [41], along with exposure and confounder variables and results will be combined using Rubin’s rules. STATA 16 will be used for all analyses.

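### The imputation rule names only cancer death as its outcome; applied as written to the cardiovascular and VTE analyses it omits the analysed event and leaves some confounding in place

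*Protocol article*

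**What the plan says.** The last paragraph of Statistical analysis in the Protocol article sets the approach to missing data: "In general, multiple imputation will be used to impute missing values particularly for stage, smoking and BMI". It then names the content of the imputation models: "As recommended cancer-specific death status and cumulative hazard will be included in imputation models [41], along with exposure and confounder variables". No other outcome is named as a predictor.

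This paragraph follows the description of the secondary outcomes, which are handled in two ways:
- All-cause mortality and second cancers: "The primary analysis strategy will be repeated for the secondary outcome of all-cause mortality and second cancers".
- Cardiovascular disease and VTE: "A different analysis strategy will be used to investigate the secondary outcome of cardiovascular disease and VTE". This strategy compares current and past HRT use with non-use, "adjusting for the confounders mentioned previously".

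The model for HRT after diagnosis is described as "adjusting for age, year, ethnicity, stage, cancer treatment, grade, comorbidities, prior hysterectomy/oophorectomy, medication use (as time-varying covariates) and deprivation". Stage is in that list; smoking and BMI are not. Smoking and BMI enter an additional analysis confined to the Welsh data.

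**The concern.** An imputation model should contain the outcome of the analysis it serves. For a Cox model, that means the event indicator and the cumulative hazard of that event. The plan follows this principle for cancer death.

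If the same imputation model serves a cardiovascular or VTE analysis, missing covariate values are drawn without reference to whether the woman had that event. In those records the covariate is related to the event only through HRT, cancer death and the other confounders. Its coefficient is pulled towards zero, so the HRT hazard ratio moves part of the way back to its value without adjustment for that covariate. Rubin's rules do not repair this, and the confidence interval does not show it.

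These are safety outcomes. The Background singles out VTE because cancer patients are already at raised risk, and the Discussion says the results should inform decisions on the safety of HRT.

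**Working it through.** **1. What the text fixes for each outcome**

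| Outcome | Strategy | Outcome terms stated for imputation | Analysed event included? |
|---|---|---|---|
| Cancer-specific death | Primary | Cancer death and its cumulative hazard | Yes |
| All-cause mortality, second cancers | Primary strategy repeated | None separately | Yes, if repeating means substituting the outcome throughout |
| Coronary heart disease, stroke, VTE | Different strategy | None separately | Not as written |

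**2. The plan's own figures.** The article states no figure for missing data or imputation. Its 7% HRT use, taken from Sample size calculation, is used below. That input reproduces the stated colorectal power by Schoenfeld's formula, power = Φ(√(d·p·(1−p))·|ln HR| − 1.960):
- √(6820 × 0.07 × 0.93) = 21.07
- 21.07 × ln 1.15 = 2.945
- Φ(2.945 − 1.960) = 83.8%, which agrees with the stated power of over 80%.

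The concern does not depend on this result.

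**3. Simulation of the mechanism.** Apart from the 7%, every parameter is an assumption:
- 20,000 women, 60 replicates, 5 imputations
- one binary confounder with 30% prevalence, odds ratio 0.5 with HRT, hazard ratio 1.5 for cancer death and 1.5 or 2.5 for CVD
- true HRT hazard ratio for CVD of 1.0
- cancer death at a baseline rate of 0.08 and CVD at 0.02 per unit time; end of follow-up uniform between 3 and 10
- confounder missing completely at random in 10%, 20% or 40%
- logistic imputation on HRT, cancer-death indicator and its Nelson-Aalen hazard, without or with the CVD indicator and its Nelson-Aalen hazard.

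The measure is residual share = (log HR after imputation − log HR with complete data) / (log HR unadjusted − log HR with complete data). Each difference column below is a log hazard ratio for HRT minus its complete-data adjusted value.

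| Missing | Confounder–CVD HR | Unadjusted | Cancer death only | HRT HR implied | Residual share | CVD terms added | Residual share |
|---|---|---|---|---|---|---|---|
| 10% | 1.5 | −0.0523 | −0.0052 | 0.995 | 10% | 0.0000 | 0% |
| 10% | 2.5 | −0.1303 | −0.0131 | 0.987 | 10% | 0.0009 | −1% |
| 20% | 1.5 | −0.0528 | −0.0108 | 0.989 | 20% | 0.0001 | 0% |
| 20% | 2.5 | −0.1271 | −0.0246 | 0.976 | 19% | 0.0012 | −1% |
| 40% | 1.5 | −0.0505 | −0.0187 | 0.981 | 37% | 0.0023 | −4% |
| 40% | 2.5 | −0.1311 | −0.0547 | 0.947 | 42% | −0.0028 | 2% |

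Example, last row: 0.0547 / 0.1311 = 42%, and exp(−0.0547) = 0.947. Shares were computed before rounding. Standard errors are 0.0003 to 0.0014 for the cancer-death-only differences and 0.0004 to 0.0016 with the CVD terms added.

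The residual share roughly equals the missing fraction. Adding the analysed event and its hazard brings it to about zero.

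**4. Which variables are affected.** Of the three variables singled out for imputation, only stage is in the listed adjustment set that the cardiovascular and VTE models inherit. Smoking and BMI matter where the Welsh-only adjustment is applied to these outcomes. Any other confounder with missing values is affected in the same way.

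**The case against.** The strongest reply is that the sentence says what will be included and does not say that nothing else will be. It does not say that one imputed dataset serves every analysis. It cites a recommendation and may simply illustrate it with the primary outcome, as a condensed article might. A reader might infer that the plan deliberately bars other outcomes from the imputation models; the text does not support that.

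For all-cause mortality and second cancers the reply largely succeeds. Repeating the primary strategy for a new outcome can naturally mean substituting that outcome in the imputation model as well.

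It does not succeed for cardiovascular disease and VTE. These are expressly given a different strategy, and the only imputation rule available to them names another event. That is a stated rule that does not fit the analysis, rather than a detail left out.

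A second objection is that smoking and BMI, the intuitive confounders here, are outside the listed main model and are unavailable in Scotland. This stands. It narrows the effect in the pooled models chiefly to stage, and the article gives no basis for judging how strongly stage confounds HRT with cardiovascular events. The simulation uses a generic confounder, so it does not answer that question.

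**Conclusion.** The point holds for the cardiovascular and VTE analyses. Followed as written, the imputation rule omits the analysed event and leaves part of the imputed variable's confounding in the HRT hazard ratio. The primary analysis of cancer-specific death is unaffected.

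Under the assumptions above, the share left is about 10% at 10% missing, 19–20% at 20% and 37–42% at 40%. The corresponding HRT hazard ratios run from 0.995 to 0.947 against a true 1.0. At low missingness this is negligible. The direction follows from the assumed odds ratio of 0.5, under which HRT users carry less of the risk factor and HRT looks safer than it is; an association of the opposite sign would reverse it. The simulation held HRT fixed over time and used one confounder, so it shows the mechanism and its rough scale. It does not forecast this study's bias.

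Two stronger readings are tempting and are not supported:
- A reader might infer that covariates are imputed as wholly unrelated to the secondary outcomes. They are only conditionally independent of them, given HRT, cancer death and the other confounders, and only in records with missing values.
- A reader might infer that half or more of the confounding remains. Since the residual share tracks the missing fraction, that would take missingness of around a half, and the article states no rate.

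The rule is still worth changing before analysis, because the outcomes concern safety and the remedy is simple.

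**What to change.** Replace the sentence on imputation content with a rule that applies to every outcome: each analysis uses an imputation model holding that outcome's event indicator and Nelson-Aalen cumulative hazard, alongside cancer death, exposure and confounders. The outcomes to list are all-cause death, second cancer, coronary heart disease, stroke, VTE and the combined cardiovascular outcome. This can be done with one imputation per outcome or with a single imputation holding all event indicators and hazards.

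The cost is one sentence in the plan, a few lines of code and more computing time. If the investigators already intend outcome-specific imputation, the sentence merely records it.

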### Sample size calculation

Sample size calculations were conducted based upon the number of cancer cases in published studies from Scotland [42, 43], and in Wales based upon published counts of cases from the Welsh Cancer Intelligence and Surveillance Unit assuming 90% have GP linked data (provided by SAIL databank). The number of deaths was estimated based upon survival at 6 months and 5 years from English published female survival curves [44]. In sample size calculations we estimated that 7% of female cancer patients would use HRT after diagnosis similar to published reports (e.g. 5% of a Swedish colorectal cancer cohort used HRT after diagnosis [25], and 9% of a Danish melanoma cohort used HRT after diagnosis [26]).

For instance, we estimate there will be 22,000 colorectal cancer cases diagnosed in Scotland (diagnosed 2009 to 2016) and Wales (diagnosed 2000 to 2016), of whom, approximately 20% (4400) will die within 6 months (and be removed from analysis of HRT after diagnosis) and a further 31% (6820) will die within 5 years. Therefore, based on a cohort of 17,600 colorectal cancer patients and 6820 cancer-specific deaths, we would have over 80% power to detect, as significant at the 5% level, a HR for cancer-specific mortality of 1.15 (or 0.85) for HRT users after diagnosis (i.e. we could detect an increased risk of cancer-specific mortality in HRT users of 15%) using Schoenfeld’s method [45]. Similarly, in gastric cancer patients, we anticipate 3300 patients and 1181 cancer-specific deaths in the analysis of HRT after diagnosis and therefore we would have over 80% power to detect, as significant at the 5% level, a HR for cancer-specific mortality of 1.45 for HRT users after diagnosis. A similar analysis is being conducted in England using QResearch and we anticipate pooling results across the three cohorts which will further increase power.

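### The colorectal power statement uses ever-use of HRT (7%) where the lagged, time-varying analysis needs the exposed share at the death times, and the margin for HR 1.15 is thin

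*Protocol article*

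**What the plan says.** The Sample size calculation section sets one exposure figure for all cancer sites: "In sample size calculations we estimated that 7% of female cancer patients would use HRT after diagnosis similar to published reports". Two reports are given as examples. One is that "5% of a Swedish colorectal cancer cohort used HRT after diagnosis"; the other is 9% in a Danish melanoma cohort.

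The worked example is colorectal cancer, "based on a cohort of 17,600 colorectal cancer patients and 6820 cancer-specific deaths", and by Schoenfeld's method the authors state that "we would have over 80% power to detect, as significant at the 5% level, a HR for cancer-specific mortality of 1.15", or 0.85 in the other direction. A second example gives gastric cancer over 80% power at HR 1.45 with 1181 deaths.

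The Statistical analysis section defines exposure for the same analysis. Follow-up begins 6 months after diagnosis, HRT is time-varying, and "patients will be considered non-users and then users after a lag of 6 months after their first HRT prescription".

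**The concern.** For a binary exposure, the information in Schoenfeld's formula is D × p(1 − p), where D is the number of deaths and p is the proportion exposed. With a fixed exposure and a hazard ratio near 1, p is simply the proportion of the cohort exposed. With a time-varying exposure, p has to be the share of women at risk who count as exposed when deaths occur.

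The article supplies the proportion who use HRT at any time after diagnosis. Under its own definition these women contribute unexposed time until the lag has run, and a user who dies before then counts as an unexposed death. For a given level of ever-use the average exposed share at the death times is therefore lower. The section mentions no allowance for this.

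At stake is how the study's sensitivity to harm is described. The article tells readers that a 15% increase in cancer-specific mortality could be detected, and its Discussion offers the results as evidence on safety. If the stated power is too high in the direction of harm, a null colorectal result may look more reassuring than it is.

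**Working it through.** **Inputs.** From the Sample size calculation section: D = 6820 (colorectal) and 1181 (gastric); HR 1.15 or 0.85 (colorectal) and 1.45 (gastric); 5% level; 7% ever-use. From the Statistical analysis section: follow-up from 6 months after diagnosis and a 6-month lag after first prescription. Sidedness is not stated; I assume two-sided.

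**Formulas.**
- Power = Φ(|ln HR| × √(D p(1 − p)) − 1.96)
- Deaths needed for 80% power = (1.96 + 0.8416)² / [p(1 − p)(ln HR)²]
- HR detectable with 80% power = exp(2.8016 / √(D p(1 − p)))

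**Step 1: reproduce the plan's figure.** At p = 0.07, D p(1 − p) = 6820 × 0.0651 = 444.0, with square root 21.07. For HR 1.15, 0.1398 × 21.07 = 2.945, and Φ(2.945 − 1.96) = 83.8%. For HR 0.85, 0.1625 × 21.07 = 3.424, giving 92.8%. For gastric HR 1.45, 0.3716 × √(1181 × 0.0651) = 3.258, giving 90.3%. All three agree with the stated over 80%.

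**Step 2: vary the exposed share at the death times.**

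| Exposed share | Power, HR 1.15 | Deaths needed, HR 1.15 | 80%-power HR, colorectal | Power, HR 0.85 | Power, gastric HR 1.45 |
|---|---|---|---|---|---|
| 7% | 83.8% | 6173 | 1.14 | 92.8% | 90.3% |
| 6% | 78.3% | 7125 | 1.15 | 89.0% | 85.8% |
| 5% | 71.1% | 8460 | 1.17 | 83.3% | 79.5% |
| 4% | 61.9% | 10,465 | 1.19 | 74.9% | 70.6% |

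**Step 3: break-even.** Setting power to 80% with 6820 deaths requires p(1 − p) = 7.849 / (6820 × 0.1398²) = 0.0589, so p = 6.29% for HR 1.15. That is 6.29/7 = 90% of the assumed figure: losing a tenth of the exposure uses up the margin. For HR 0.85 the break-even is 4.57%; for gastric HR 1.45 it is 5.07%.

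**Step 4: what the lag does when ever-use is held at 7%.** The article does not say when users start, so the mixes here are assumptions. Deaths follow a Weibull curve through 80% alive at 6 months and 49% at 5 years, from the article's 20% and 31%. A given fraction of users have their first prescription evenly over the first 3 months after diagnosis, and the rest start evenly over 5 years. Each becomes exposed 6 months after first prescription. Power uses the mean of p(1 − p) over the death times.

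| Users starting within 3 months | Mean exposed share | Power, HR 1.15 | Power, HR 0.85 |
|---|---|---|---|
| 100% | 6.5% | 81.3% | 91.2% |
| 75% | 5.5% | 74.7% | 86.3% |
| 50% | 4.5% | 66.0% | 78.8% |

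A variant in which 7% is the realised ever-use in a simulated cohort with 6820 deaths among 17,600 women gives exposed shares of 6.6%, 5.9% and 5.2%, and power of about 82%, 77% and 73% for HR 1.15. The two calculations agree in direction and differ in size.

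**The case against.** A reader might infer that the power calculation is wrong, or that 80% power is not available. The document supports neither. Every stated figure reproduces at 7%. The exposed share at the death times is not given, so any shortfall is conditional.

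The lag alone need not break the claim. Follow-up also starts 6 months after diagnosis, so a woman who continues HRT from diagnosis is exposed almost from the start, and if all users are of this kind power remains about 81%. The loss comes from later starters. The article plans a new-user analysis and one on the timing of initiation after diagnosis, so later starters are expected, but it does not say how many.

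It is also tempting to treat 5% as the study's own colorectal estimate. It is one published example from another country, set beside 9% for melanoma, and 7% is the authors' estimate for all sites. At 9% exposed, power for HR 1.15 would be 91%. Still, 5% is the only colorectal figure cited, and the article does not explain why the colorectal example uses a higher one.

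The gastric statement might be read as inconsistent because HR 1.45 has 90% power at 7%. It is true as written, and conservative at that share.

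The death count is uncertain in both directions. Deaths beyond 5 years among early Welsh cases would add events, while women diagnosed in 2015 and 2016 have less than 5 years to the end of follow-up in 2019. At 6% exposed, 7125 deaths (about 4.5% more than 6820) would restore 80% power. Pooling with the English cohort is anticipated, but the stated claim covers two cohorts.

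Finally, this is a study of existing records. No recruitment target depends on the calculation, and the results will carry confidence intervals. That limits the consequence; it does not make ever-use the right input.

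**Conclusion.** The point stands as a moderate issue about a planning input. The stated power for colorectal HR 1.15 treats ever-use after diagnosis as a fixed baseline exposure, while the planned analysis is time-varying and lagged. The average exposed share at the death times is below 7%, and the claim fails once it is under about 6.3%.

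At 5% exposed, power is 71% and the 80%-power hazard ratio is 1.17. With 7% ever-use, power is about 81% to 82% if all users start within 3 months of diagnosis, about 75% to 77% if three-quarters do, and about 66% to 73% if half do. HR 0.85 is more robust, and gastric HR 1.45 becomes borderline only near 5%.

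These figures take 6820 and 1181 deaths as given and assume a two-sided 5% test. The start-time mixes are illustrative.

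**What to change.** In the Sample size calculation section, base the power on the expected exposed share at the death times after the 6-month lag, state the assumption about when users start, and show a range of shares that includes the cited 5%; 4% to 7% would serve. For example: with 6820 colorectal deaths and 5% exposed at the death times, there is 80% power for HR 1.17 and 71% for HR 1.15.

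Give the gastric figures over the same range: with 1181 deaths, the 80%-power hazard ratio is about 1.38 at 7%, 1.41 at 6%, 1.45 at 5% and 1.52 at 4%.

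This means rewriting one paragraph. It needs no new data and does not change the analysis. The cost is that the stated detectable hazard ratios become slightly less favourable.

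### The 6,820 colorectal deaths used for power are first given without a cause and then called cancer-specific; if they are all-cause deaths, the power claim for HR 1.15 has little margin.

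*Protocol article*

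**What the plan says.** In the protocol article, the Sample size calculation section describes its source for deaths as follows: "The number of deaths was estimated based upon survival at 6 months and 5 years from English published female survival curves". For colorectal cancer it starts from 22,000 cases, removes 20% (4,400) as deaths in the first 6 months, and then states that "a further 31% (6820) will die within 5 years". No cause of death is attached to either count. The next sentence bases the power statement on the same figure under another name: "based on a cohort of 17,600 colorectal cancer patients and 6820 cancer-specific deaths". With these inputs the section claims over 80% power for "a HR for cancer-specific mortality of 1.15 (or 0.85) for HRT users after diagnosis".

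The Outcome section restricts the primary event to deaths with cancer as underlying cause. The Statistical analysis section follows women to that event, "censored on death from other causes or end of follow-up", and excludes women who died of any cause in the first 6 months. All-cause mortality is a separate, secondary outcome.

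**The concern.** One number serves as two quantities. Deaths read off a survival curve become primary events with no deduction and no reason given for treating the two as equal. The cohort includes women aged 40 to 79, so some deaths between 6 months and 5 years will be from other causes, and the primary analysis will censor them.

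For a given hazard ratio and share of users, Schoenfeld's power is driven by the number of events. If 6,820 contains censored deaths, the stated power rests on events that the primary model will not count. The claim for HR 1.15 matters most, because it concerns the harmful direction and is the one the section spells out as a 15% increase in risk.

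**Working it through.** **Inputs, all from the Sample size calculation section unless marked.**
- Cases: 22,000. Deaths by 6 months: 20%. Further deaths by 5 years: 31%.
- Share of users p: "we estimated that 7% of female cancer patients would use HRT after diagnosis", so p(1 − p) = 0.07 × 0.93 = 0.0651.
- Test: "as significant at the 5% level". Sidedness is not stated; two-sided is assumed, so z = 1.96.
- Gastric example: 1,181 events, HR 1.45.
- Cancer share of deaths: not in the document. A range is assumed.

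**Counts.** 22,000 × 0.20 = 4,400; 22,000 − 4,400 = 17,600; 22,000 × 0.31 = 6,820. All reproduce, and they show that 6,820 is the full 31% with nothing removed.

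**Stated power.** Power = Φ(√(D × 0.0651) × |ln HR| − 1.96).
- Colorectal, HR 1.15: √(6,820 × 0.0651) = 21.07; 21.07 × 0.1398 − 1.96 = 0.985; power 83.8%.
- Colorectal, HR 0.85: 21.07 × 0.1625 − 1.96 = 1.464; power 92.8%.
- Gastric, HR 1.45: √(1,181 × 0.0651) = 8.77; 8.77 × 0.3716 − 1.96 = 1.298; power 90.3%.

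All three agree with the plan's claim of over 80%, given its event counts.

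**Events needed for 80% power.** D = (1.96 + 0.8416)² / (0.0651 × (ln HR)²).
- HR 1.15: 6,173, which is 90.5% of 6,820. The claim tolerates about 9.5% other-cause deaths (6,820 − 6,173 = 647).
- HR 0.85: 4,565, which is 66.9% of 6,820. It tolerates about 33%.
- Gastric, HR 1.45: 874, which is 74.0% of 1,181. It tolerates about 26%.

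**Effect of an assumed cancer share.** Detectable HR = exp(2.8016 / √(D × 0.0651)), at 80% power.

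| Cancer share (assumed) | Colorectal events | Power, HR 1.15 | Detectable HR | Power, HR 0.85 | Gastric events | Power, HR 1.45 |
|---|---|---|---|---|---|---|
| 100% | 6,820 | 83.8% | 1.142 | 92.8% | 1,181 | 90.3% |
| 95% | 6,479 | 81.9% | 1.146 | 91.6% | 1,122 | 88.8% |
| 90% | 6,138 | 79.8% | 1.150 | 90.1% | 1,063 | 87.1% |
| 85% | 5,797 | 77.5% | 1.155 | 88.4% | 1,004 | 85.2% |
| 80% | 5,456 | 75.0% | 1.160 | 86.5% | 945 | 83.0% |
| 70% | 4,774 | 69.3% | 1.172 | 81.7% | 827 | 77.8% |

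**Does either reading of the curves make the paragraph consistent?** The same curves supply both the 6-month and the 5-year figures.
- Overall survival: 4,400 is the right kind of count, because the analysis excludes deaths from any cause in that period. Then 6,820 is all-cause and too high as a count of primary events within 5 years.
- Net or cause-specific survival: 6,820 is approximately the right kind of count. Then 4,400 omits early deaths from other causes, and 17,600 is too large.

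On either reading, one of the two counts is the wrong quantity.

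**The case against.** A reader might infer that the number of primary events and the power are shown to be overstated. The document does not support that, for two reasons.

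First, it does not say whether the curves are overall, net or cause-specific. With net or cause-specific curves, 6,820 is already close to a count of cancer deaths and the main fault in the event count is loose wording. This stands, although that reading moves the problem to the exclusion count.

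Second, the count stops at 5 years, whereas Table 1 gives 2019 as end of follow-up for diagnoses from 2000 (Wales) and 2009 (Scotland) to 2016. Cancer deaths after year 5 are left out, which understates events. Women diagnosed after 2014 have less than 5 years, which works the other way. The net direction for total events cannot be determined from the document. This also stands, but the plan does not offer later follow-up as its reason for equating the two counts.

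A reader might also infer that all the power statements fail, or that the error is worse at sites with low cancer fatality. The HR 0.85 and gastric claims stay above 80% at every assumed share from 80% upwards. The gastric 1,181 is only ever described as cancer-specific, so no relabelling is visible there. No figures are given for other sites.

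Finally, the cohort size is set by registry cases, not by a recruitment target, so the calculation describes precision and does not drive the design.

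**Conclusion.** The concern holds in a limited form. The section uses 6,820 for two different quantities, and no single reading of its source makes both 4,400 and 6,820 correct.

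If the curves are overall survival, the 5-year count of primary events is too high, and the claim for HR 1.15 fails once more than about 9.5% of those deaths are from other causes. The shift is modest: across assumed cancer shares from 95% to 80%, power runs from 81.9% to 75.0%. The detectable HR rises from 1.142 with no deduction to 1.150 at a 90% share and 1.160 at 80%.

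These figures rest on 7% users, a two-sided 5% level and assumed cancer shares. With a one-sided test, power for HR 1.15 at 6,820 events would be 90.3%. The point deserves correction because a stated power figure for the primary outcome depends on a mislabelled input, not because the study is shown to be too small.

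**What to change.** 1. State which survival measure the published curves give.
2. If it is overall survival, multiply expected deaths by a cancer share specific to each site, give the source of that share, and restate events, power and detectable HR. Keep 6,820 only as the all-cause count.
3. If it is net or cause-specific survival, say so, correct the wording that these women will die, and recompute the deaths from any cause in the first 6 months and the resulting cohort size.
4. In both cases, base the event count on actual follow-up to 2019 by year of diagnosis instead of a flat 5 years, since this could move the total either way.
5. State whether the 5% level is two-sided, and confirm how the gastric 1,181 was obtained.

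The cost is a recalculation and perhaps a slightly less favourable stated figure. No change to the design, data or analysis is needed.
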